### Study setting and procedures

2.2

The experiments will involve a seated overhand throwing task using the nondominant hand, which should render the task novel for the participants (Iwatsuki and Regis, 2021) and suitable for examining changes during the learning phase (Solum et al., 2020). All procedures will be conducted in a dedicated laboratory room with a fixed layout (i.e., equipment will be positioned in the same orientation for every participant) and free from external distractions such as noise or foot traffic. All mobile phones in the room will be in silent mode, and fluorescent lighting and temperature will remain constant throughout all the sessions. A participant will be seated on a stool at a prescribed distance from the middle of a circular target on the wall. On the basis of previous related studies, the distance to the target is 3 m for both children (Ávila et al., 2012) and older adults (Chiviacowsky et al., 2009). Our related study revealed that a distance of 4 m was suitable for young adults, who may arguably have greater physical capacity than children and older adults do (Capio and Eguia, 2025). The research staff will be trained to precisely follow a written protocol that details the standardized instructions for participants, order of task trials, rest periods, and data collection procedures. All equipment will be calibrated before each use to ensure identical settings for all participants.

Each experiment will be conducted over 2 days with 1 day in between, and it will consist of a pretest, a learning phase, and a posttest, as illustrated in Figure 1. The learning phase consists of two practice sessions. In each session, participants will perform 10 blocks of 15 practice trials per block, with two-minute rest periods between blocks (i.e., 150 practice trials per session). The occurrence of practice errors can be influenced by manipulation of task constraints, such as target size (Capio et al., 2013b; van Ginneken et al., 2018). As such, the practice conditions for the EL group consists of a circular target with a 100 cm radius which will be used in the first two blocks of practice; the target radius progressively decreases by 10 cm (i.e., 100 cm, 90 cm, 80 cm… 20 cm, 10 cm) after every two blocks. Thus, the target radius in the first practice session decreases from 100 cm to 60 cm, and in the second practice session, it decreases from 50 cm to 10 cm. The practice condition for the EF group consists of a circular target with a 10 cm radius which will be used throughout all practice sessions.

**Figure 1 fig1:**
[figure not shown]
Schematic diagram of the study procedures.

In the test phases (i.e., pretest and posttest), the target consists of 10 concentric circles with radii that increase from 10 cm to 100 cm (in increments of 10 cm). Hitting the innermost ring corresponds to the highest possible score per trial (i.e., 100 points). The score is reduced by 10 points for each ring that is incrementally more distant from the center; a score of zero is given for throws that fail to hit any part of the target. A similar task has been used in previous motor learning studies (Chiviacowsky et al., 2012). See Figure 2 for an illustration.

**Figure 2 fig2:**
[figure not shown]
Diagram of the overhand throwing task in the test phase.

The pretest will be conducted on the first experimental day, immediately prior to the first practice session. It will consist of one practice trial, followed by 10 trials without any instruction or feedback (apart from being told to aim for the highest score). The posttest will be conducted on the second experimental day, immediately following the second practice session. We will adopt an A-B-A design (retention-transfer-retention) as used in motor learning studies (Maxwell et al., 2017). The first retention test will evaluate performance after the training phase; the transfer test will verify whether cognitive resources are required to support motor performance; the second retention test will assess whether any difference in performance in the transfer test was due to continued learning. The retention tests will consist of one practice trial followed by 10 trials (i.e., identical to the pretest). The transfer test consists of 10 trials with a concurrent cognitive task of counting backward (e.g., Capio et al., 2013b). The counting backward task will vary as a function of differences in cognitive ability that are associated with age. Children are asked to count backward from 100 in one (e.g., 100, 99, 98…), whereas older adults are asked to count backward from a randomly selected starting point in three (e.g., 95, 92, 89…).

Procedures for monitoring protocol adherence will include the use of attendance logs and reminders before each block to encourage engagement. We expect minimal risk of dropouts because participation will be completed within two sessions. Nevertheless, missed appointments for the second session will be followed up and rescheduled within 2 days of the original schedule. Because post-tests will be administered in the second session, participants who completely miss the said session will be excluded from data analysis. There are no requirements regarding concomitant care, but participants will be asked to report any activities that involved a similar throwing task in the day(s) intervening the two study sessions. Any deviation from the protocol, including those due to technical issues, and related concomitant care will be documented for each participant.

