We hypothesize that the changes during the learning phase significantly differ between errorless and errorful learning conditions for (i) movement variability, (ii) perceived competence, and (iii) PFC activity. We further hypothesize that the changes across the same variables and task performance significantly differ from before to after practice between errorless and errorful learning conditions. Finally, we will test whether the changes in task performance from before to after practice are moderated by movement variability, perceived competence, or PFC activity.

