We will use random effects multilevel/hierarchical linear model (HLM) analysis to test our hypotheses. To test changes in the learning and test phases, we use the HLM approach to estimate growth curve models to examine change over time (i.e., practice blocks, test) on two levels—level one representing individual change over time and level two accounting for the extent to which change differs between age groups and between the EL and EF groups (Raudenbush and Bryk, 2002). The level one model will quantify individual changes in the measured variables (i.e., task performance, movement variability, perceived competence, PFC activity) as a function of time (i.e., practice block, test). Random slopes and intercepts will be specified for participants to account for individual differences in baseline performance and rate of change. For the level two model, fixed effects will include age group (i.e., children, older adults) and learning condition (i.e., EL, EF) as categorical predictors. Additional fixed effects will include the relevant covariates (i.e., cognitive processing speed and executive function). The random effects of the repeated measures estimate the relationship of the scores at the first time point to the rate of change over time. Planned interactions will include age group × learning condition to examine different effects of the learning condition across age groups and time × learning condition to test whether learning trajectories vary between the EL and EF conditions. Separate models will be fitted to each of the measured variables.

The statistical assumptions underlying HLM (i.e., normality of residuals, homoscedasticity, and independence of random effects) will be evaluated through diagnostic plots and residual analysis. If violations are detected, robust estimation methods or appropriate variable transformations will be applied. Missing data will be handled through maximum likelihood estimation under the assumption of missing at random (MAR) to retain all available data and minimize bias. Our data analysis approach is deemed appropriate because it allows us to track change over repeated measures and account for participants’ individual patterns of change by calculating estimates of within- and between-individual variation (O’Connell and McCoach, 2004).

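### Excluding everyone who misses session 2 from all analysis discards usable session 1 data and conflicts with the maximum-likelihood plan; the reason given does not reach the learning-phase models

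*Protocol article*

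**What the plan says.** Section 2.2 (Study setting and procedures) provides for missed second sessions to be rescheduled within two days. It then states: "Because post-tests will be administered in the second session", "participants who completely miss the said session will be excluded from data analysis". The exclusion is not limited to particular outcomes or models.

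Section 2.6 (Data processing and analysis) states: "Missing data will be handled through maximum likelihood estimation under the assumption of missing at random (MAR) to retain all available data and minimize bias". The models to which this applies "estimate growth curve models to examine change over time (i.e., practice blocks, test) on two levels", so practice-block data are outcomes in their own right.

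The first hypothesis in section 1.4 concerns practice, not the posttest: "We hypothesize that the changes during the learning phase significantly differ between errorless and errorful learning conditions", for movement variability, perceived competence and PFC activity.

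**The concern.** In a two-session study, missing the second session is the most obvious way to lose a participant's data. Section 2.2 takes exactly that case away from the missing-data method adopted in section 2.6.

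Two things are at stake.

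- **Lost information.** The learning-phase models can use session 1 data without any posttest. The exclusion discards half of the planned practice record for each participant affected.
- **Possible bias.** Attending session 2 is a post-randomisation event. In session 1 the EL arm throws at targets of 100 to 60 cm radius and the EF arm at 10 cm throughout. The introduction argues that early success raises perceived competence and motivation. If discouraged EF participants return less often, the EF participants left in the analysis are a selected group. Perceived competence is also an outcome and a planned moderator, so the selection could act on a variable under study.

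**Working it through.** **1. What a participant without session 2 has already supplied**

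| Data | Source | In hand after session 1 |
|---|---|---|
| Pretest | 2.2: "The pretest will be conducted on the first experimental day, immediately prior to the first practice session" | 1 test of 10 trials |
| Hits | 2.2: "participants will perform 10 blocks of 15 practice trials per block" | 10 of 20 blocks (150 of 300 trials) |
| Kinematics, PFC | 2.3: pretest and blocks 3 to 8 of each session | pretest + 6 of 12 practice blocks |
| Perceived competence | 2.3: after the pretest, and after blocks 3 and 8 of each session | 3 ratings |

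The cognitive covariates are left out of the table because section 2.3 does not say when they are measured.

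**2. The plan's own figures**

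Section 2.1 needs 46 per age group (effect size 0.23, 80% power, alpha 0.05) and recruits 52. Reading 0.23 as f² in a regression F test with two tested predictors and noncentrality 0.23 × N, power is 0.7997 at N = 45 and 0.81 at N = 46, so 46 is reproduced. Then 46 / 0.90 = 51.1, rounded up to 52. The sample size is not in question. The allowance is 52 − 46 = 6 per age group (6/52 = 11.5%), to cover both attrition and data loss in both arms.

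**3. Adverse scenario**

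Assumptions, since the protocol gives none of these: 26 per arm; the k weakest EF participants on session 1 performance do not return; no EL participant is lost; normal scores in SD units. Let m(k) be the mean of the 26 − k who remain. By simulation, m(3) = 0.21 and m(6) = 0.38.

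- Shift in the EF session 1 mean: m(k).
- Shift in the EF posttest mean: r_post × m(k).
- Shift in EF pre-to-post change: (r_post − r_pre) × m(k).

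Here r_post and r_pre are the correlations of session 1 performance with posttest and pretest. With r_pre = 0.6:

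| Shift in EF arm (SD) | r_post 0.4 | r_post 0.6 | r_post 0.8 |
|---|---|---|---|
| Posttest, k = 3 | 0.08 | 0.13 | 0.17 |
| Posttest, k = 6 | 0.15 | 0.23 | 0.30 |
| Change, k = 3 | −0.04 | 0 | +0.04 |
| Change, k = 6 | −0.08 | 0 | +0.08 |

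Change is much less affected than the posttest because removing weak performers also raises the retained pretest mean.

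**4. Less extreme dropout, and what maximum likelihood recovers**

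A large simulation (400,000 per arm) assumed a true EL−EF difference of 0.5 SD and about 11.5% dropout overall, depending on session 1 performance. Dropout was split EL/EF as 11.5%/11.5%, 4%/19% or 0%/23%. Three sets of correlations between 0.3 and 0.7 were used.

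| Quantity (true value 0.5) | Completers only | All available data |
|---|---|---|
| Session 1 difference | 0.24 to 0.51 | about 0.50 (fully observed) |
| Posttest difference | 0.32 to 0.50 | – |
| Pre-to-post change | 0.40 to 0.51 | 0.49 to 0.51 |

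Completers-only stayed at about 0.50 whenever dropout was unrelated to performance, or depended on it equally in both arms at equal rates. The maximum-likelihood result for change used session 1 performance within each arm, and that is what protects it. A model with pretest and posttest alone would gain little.

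**The case against.** The strongest reply is that the two rules have different jobs: section 2.2 defines the analysis set, and section 2.6 deals with gaps inside it, such as lost fNIRS recordings or missed blocks. Section 2.1 itself separates attrition from data loss. This reading is possible, so a reader who infers that the two statements are logically incompatible goes too far. It does not remove the problem. It still sits badly with a stated aim of retaining all available data, and the reason given for the exclusion still does not touch the learning-phase models.

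Three further objections stand.

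- **Non-return that differs by arm is not documented.** It is plausible on the protocol's own theory. However, no rate by arm is given, and participants are not told that another condition exists.
- **Dropout is expected to be minimal**, and missed appointments are rescheduled. Six losses in one arm would be 6/26 = 23% of that arm and would use the whole allowance for the age group.
- **Session 1 hits are not one common variable.** They are scored on 100 to 60 cm targets in EL and a 10 cm target in EF, so they cannot enter a test-phase model as a single pooled auxiliary.

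A reader might also infer that the planned comparison is off by 0.13 to 0.30 SD. The documents do not support that. Those values are worst-case shifts in the EF posttest mean, whereas the hypothesis concerns pre-to-post change. Nor can the shift safely be expressed as a share of the planning effect, because section 2.1 does not name the metric of 0.23.

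**Conclusion.** The point holds, as something that should be fixed rather than a fatal flaw. The exclusion is wider than its stated reason, conflicts with the missing-data plan, and discards session 1 data that the learning-phase hypothesis can use.

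Bias is possible but conditional: non-return must be related to performance or perceived competence and must differ by arm. Its size is unknown and probably small with minimal dropout. It would be largest for session 1 outcomes, and near zero to modest for pre-to-post change: within about ±0.08 SD in the adverse scenario, and at most about 0.10 SD (0.50 to 0.40) in the simulation. All of these figures rest on assumed correlations and dropout patterns. The documents do not show that the randomised comparison of change will be materially distorted.

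**What to change.** Replace the exclusion sentence in section 2.2 with an analysis-set statement and align section 2.6 with it:

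- Analyse all randomised participants with any outcome data in the arm assigned. Session 1 data enter the learning-phase maximum-likelihood models, and the pretest enters the test-phase models.
- If session 1 performance is used as an auxiliary variable in the test-phase models, use it within arm or with an arm interaction, because target size differs by arm.
- Keep the completers-only analysis as a sensitivity analysis.
- Report session 2 non-attendance by arm, with reasons.

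The cost is one sentence replaced and a few added. Sample size, procedures and data collection do not change. The rule should be settled before analysis, since two analysts following different sections would otherwise analyse different populations.

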### Outcome measures

2.3

The outcome measures consist of task performance, movement variability, perceived competence, and PFC activity. Covariate measures include cognitive processing speed and executive function capacity.

Task performance during the learning phase is measured by the number of successful hits on the target in each block. Task performance during the test phase is measured by accuracy scores. Task performance scores will be measured in real time by two independent observers and verified *post hoc* using video recordings of the target. The range of scores for successful hits during learning is 0–15 per block, and the ranges for accuracy during the tests are 0–100 per trial and 0–1000 for each test (Capio and Eguia, 2025).

Movement variability will be calculated using the coefficient of variation (CV) of the joint angles and joint velocity. CV is defined as the standard deviation divided by the mean (expressed as a percentage) and provides a normalized measure of how consistently joint kinematics are maintained across repeated movements (Mukherjee and Yentes, 2018). Movement kinematics will be generated using the Noraxon MyoMOTION system (Noraxon Inc., United States), which uses inertial measurement units (IMUs) to track the three-dimensional angular changes in the upper limb used for throwing. This instrument has been shown to provide valid estimates of joint kinematics (Heuvelmans et al., 2025). Four IMUs will be positioned on the (i) dorsum of the hand, (ii) dorsal side of the distal half of the forearm, (iii) lateral side of the middle third of the upper arm, and (iv) over the spine of the upper thoracic region.

Perceived competence will be measured using the corresponding IMI subscales, including adapted versions for older adults (Iwatsuki and Regis, 2021) and children (Ávila et al., 2012). The IMI uses a 7-point Likert scale (i.e., 1 = “not at all true”; 7 = “very true”). The perceived competence subscale includes statements such as “I think I am pretty good at this task,” “I was pretty skilled at this task,” and “This was a task that I could not do very well.” IMI subscales, including perceived competence, have been shown to have adequate internal consistency in the context of laboratory movement experiments (McAuley et al., 1989). While the IMI subscales have not been formally validated in our target participants, they have been used widely in motor learning studies, including those of children (Goudini et al., 2019; Levac and Lu, 2019; Drews et al., 2020) and older adults (e.g., Kappen et al., 2020; Iwatsuki and Regis, 2021; Dong et al., 2023).

PFC activity will be monitored by measurements of relative changes in oxygenated (HbO) and deoxygenated hemoglobin (HbR) levels using the Brite NIRS wireless system (Artinis Medical Systems, The Netherlands). Brite has been widely used to measure brain oxygenation in recent studies that have examined cognitive (Bhat et al., 2017) and affective (Ruotsalo et al., 2023) processes. Many studies have used the system in older adults (e.g., Goenarjo et al., 2021; Maasakkers et al., 2021; Bonnal et al., 2022) and children (e.g., Bulgarelli et al., 2023; Zheng et al., 2023; Yan et al., 2025) and have shown that it is a reliable and feasible instrument for characterizing adaptive cortical changes.

Movement kinematics and PFC activity will be measured during the pretest, across blocks three to eight in each practice session, and during the posttest. We aim to capture stable estimates of movement kinematics and PFC activity that reflect practice performance and limit the confounding effects of within-participant variability due to adaptation in the initial blocks (Eggert et al., 2021). Perceived competence will be measured after the pretest, immediately after blocks three and eight in each practice session, and after the posttest.

To account for individual cognitive processing speed and executive function capacity, we will use the Color Trails Test (CTT)-1 and -2 (Williams et al., 1995) for children and the Trail Making Test (TMT)-A and -B (Bowie and Harvey, 2006) for older adults. CTT-1 and TMT-A scores are considered measures of visual search and perceptual speed, whereas CTT-2 and TMT-B scores reflect the task-switching component of executive function. For all participants, verbal working memory will be assessed using a backward digit span test (Ramsay and Reynolds, 1995), and visuospatial working memory will be assessed using a reversed Corsi block tapping test (Corsi, 1973).

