### Underlying processes of errorless motor learning

1.3

The potential underlying processes of errorless motor learning have yet to be empirically tested. Owing to the implicit nature of errorless motor learning, it has been frequently suggested that it requires relatively low cognitive demands, as proposed by Maxwell et al. (2003). For example, despite cognitive impairments, children with intellectual disability who learn via errorless motor learning display improvements in gross motor skills and the ability to perform multiple tasks (Capio et al., 2013a). In other research involving adults without impairments, learning a novel locomotor task (i.e., split-belt treadmill walking) with few errors was found to be less dependent on cognitive resources—on the basis of reaction time to a secondary cognitive task—compared to when greater movement errors were generated (Sawers et al., 2013). Earlier studies demonstrated relatively greater conscious control by learners when they experienced more errors, as evidenced by increased coactivation of brain regions associated with movement processing (Zhu et al., 2011). As processing errors to adjust movement planning requires significant cognitive resources, the efficacy of errorless motor learning could be explained by the relatively reduced cognitive requirements. However, no study thus far has offered direct evidence that such cognitive factors differentiate errorless motor learning from learning with copious amounts of practice errors during the process of skill acquisition.

A behavioral representation of the cognitive processes during motor learning is the variability of movement, or trial–to–trial deviations of movement kinematics, which become evident when task difficulties vary (Lajoie and Franks, 1997). Movement variability may be considered to represent real-time cognitive engagement that is closely coupled with motor performance. Learners display relatively low movement variability when movement tasks demand high accuracy. A study of young adults engaged in a throwing task revealed greater movement variability during errorless motor learning than during errorful motor learning, and movement variability was negatively associated with conscious control (van Ginneken et al., 2018). These findings support the proposition that errorless motor learning is associated with relatively lower conscious control.

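### Hits per practice block follow the target schedule, so a time × condition effect on them does not show a difference in learning

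*Protocol article*

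**What the plan says.** Study setting and procedures (2.2) sets two practice schedules, each of two sessions with 10 blocks of 15 throws. For EL, "the practice conditions for the EL group consists of a circular target with a 100 cm radius which will be used in the first two" practice blocks; after every two blocks "the target radius progressively decreases by 10 cm". The article spells out the result: "the target radius in the first practice session decreases from 100 cm to 60 cm, and in the second practice session, it decreases from 50" (centimetres, ending at a radius of 10 cm). For the other arm, "The practice condition for the EF group consists of a circular target with a 10 cm radius which will be used throughout all practice sessions".

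Outcome measures (2.3) defines the practice outcome: "Task performance during the learning phase is measured by the number of successful hits on the target in each block", with a range of 0 to 15. It also fixes the recording window: "Movement kinematics and PFC activity will be measured during the pretest, across blocks three to eight in each practice session, and during the posttest".

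Data processing and analysis (2.6) lists task performance, movement variability, perceived competence and PFC activity as level-one outcomes, with time being practice block or test. Among the planned interactions is "time × learning condition to test whether learning trajectories vary between the EL and EF conditions". The added covariates are cognitive only; no term for target size is stated.

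Manipulation check (2.5) gives practice hits a separate use, which is to confirm that EL made fewer errors.

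**The concern.** A growth curve shows learning only if the outcome keeps the same meaning from block to block and from arm to arm. A hit on a 100 cm target and a hit on a 10 cm target are different events. In EL the scoring becomes harder every two blocks; in EF it never changes. The EL curve can therefore fall, and differ from EF, whatever the participants learn. A significant interaction would be reported as differing learning trajectories, with EL seeming to get worse.

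A milder form of the problem affects the process measures. Section 1.3 says "Learners display relatively low movement variability when movement tasks demand high accuracy". On that premise, a wide EL target alone predicts higher EL variability, which is also the direction that the article would take as lower conscious control.

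**Working it through.** **Block map (2.2 and 2.3).** EF is at 10 cm in every block.

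| Blocks | EL radius, session 1 | EL radius, session 2 | Kinematics and PFC recorded |
|---|---|---|---|
| 1–2 | 100 cm | 50 cm | no |
| 3–4 | 90 cm | 40 cm | yes |
| 5–6 | 80 cm | 30 cm | yes |
| 7–8 | 70 cm | 20 cm | yes |
| 9–10 | 60 cm | 10 cm | no |

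The arms share a radius in 2 of 20 blocks (session 2, blocks 9–10). Recording covers 6 × 2 = 12 practice blocks, and 0 of those 12 have a shared radius.

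**Expected hits without learning.** The article gives no throw-error SD, so σ is an assumption, varied from 20 to 50 cm. For a circular normal error centred on the target, the hit probability is 1 − exp(−r²/(2σ²)), and expected hits per block are 15 times that. Example at σ = 30 cm:

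- r = 100 cm: 15 × (1 − exp(−10000/1800)) = 14.9
- r = 60 cm: 15 × (1 − exp(−3600/1800)) = 13.0
- r = 10 cm: 15 × (1 − exp(−100/1800)) = 0.8

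Slopes are least-squares over the 20 blocks:

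| σ (cm) | EL first block | EL last block | EF, all blocks | EL slope per block | EF slope |
|---|---|---|---|---|---|
| 20 | 15.0 | 1.8 | 1.8 | −0.64 | 0 |
| 30 | 14.9 | 0.8 | 0.8 | −0.81 | 0 |
| 40 | 14.3 | 0.5 | 0.5 | −0.83 | 0 |
| 50 | 13.0 | 0.3 | 0.3 | −0.75 | 0 |

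**Expected hits with learning.** Let σ fall linearly over the 20 blocks.

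- Both arms improve equally, σ from 50 to 30 cm: slopes are −0.69 (EL) and +0.03 (EF).
- EL improves more strongly, σ from 50 to 20 cm: its slope is still −0.60.

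So the interaction is large when learning is absent or equal, and the EL slope stays clearly negative even when EL improves a good deal.

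**The case against.** **Target size is the randomised manipulation.** This stands. An EL–EF difference during practice is a valid effect of condition, so a reader who inferred that the learning-phase contrasts are invalid would go too far. What is limited is the interpretation: as learning for hits, and as reduced cognitive processing for variability and PFC activity.

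**No stated learning-phase hypothesis names hits.** This also stands. Section 1.4 names variability, perceived competence and PFC activity for the learning phase, and brings in task performance for the change from before to after practice. But 2.6 does model task performance over practice blocks and says how the interaction will be read, so the defect is in the stated analysis.

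**Matched-target evidence exists.** A reader might infer that the question of reduced cognitive processing goes unanswered. The article does not support that. Both arms face the same ring target at pretest and posttest, kinematics and PFC activity are recorded there, and the posttest includes a dual-task transfer test. These bear on cognitive demand after practice, so only the reading of the during-practice contrast is limited.

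**Accuracy demand may act through conscious control.** If so, it lies on the hypothesised pathway. That is possible, but blocks 3–8 cannot show it. The statement in 1.3 concerns variability; extending it to PFC activity is inference.

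**Blocks 9–10 are a poor substitute test.** This stands. At 10 cm EL is no longer errorless, and the posttest follows immediately. The stated reason for the window, stable estimates free of adaptation in the initial blocks, does not explain leaving out blocks 9–10, but that does not make them the right main contrast.

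**Diagnostics and transformations are planned.** They address residual behaviour and would not put the two arms on one scale.

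**Conclusion.** The point holds for hits. As written, the practice-block model of task performance would present the effect of the target schedule as a difference in learning. With equal or no learning, the EL slope is about −0.6 to −0.8 hits per block against about 0 in EF. The size rests on an assumed circular normal error with SD 20 to 50 cm; the mismatch of scale does not depend on that assumption.

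The process-measure point is secondary. In the recorded practice blocks EL throws at 90 to 70 cm and then 40 to 20 cm, against 10 cm in EF, so those contrasts carry concurrent accuracy demand. The pretest–posttest contrasts do not share either problem.

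**What to change.** 1. State in 2.6 that hits per practice block are used only for the manipulation check in 2.5, and remove them from the learning-trajectory model. Base learning claims on the pretest–posttest accuracy score, which uses one target for both arms. This costs a change of wording.
2. If a practice trajectory is wanted, score practice throws on a common metric, such as distance from centre or ring score, from the target video already planned. Give a rule for throws that land outside the filmed area. This costs scoring time and depends on the video showing where misses land, which the article does not establish.
3. Describe the blocks 3–8 contrasts of variability and PFC activity as effects of condition that include concurrent accuracy demand, and do not read them alone as reduced cognitive processing. This costs a sentence.
4. Optionally, record session 2 blocks 9–10 for the remaining participants as a supplementary matched contrast, without replacing the learning-phase test. This adds two recorded blocks. Data gathering began in August 2025, so participants already tested would lack them, and EL is no longer errorless at that radius.
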